**Table 3-1. Timepoint response: patients with target (+/-non-target) disease**

| Target lesions    | Non-target lesions          | New lesions | Overall response |
|-------------------|-----------------------------|-------------|------------------|
| CR                | CR                          | No          | CR               |
| CR                | Non-CR/non-PD               | No          | PR               |
| CR                | Not evaluated               | No          | PR               |
| PR                | Non-PD or not all evaluated | No          | PR               |
| SD                | Non-PD or not all evaluated | No          | SD               |
| Not all evaluated | Non-PD                      | No          | NE               |
| PD                | Any                         | Yes or No   | PD               |
| Any               | PD                          | Yes or No   | PD               |

| Target lesions | Non-target lesions | New lesions | Overall response |
|----------------|--------------------|-------------|------------------|
| Any            | Any                | Yes         | PD               |

CR = complete response, PR = partial response, SD = stable disease, PD = progressive disease, and NE = inevaluable.

**Table 3-2. Timepoint response: patients with non-target disease only**

| Non-target lesions | New lesions | Overall response           |
|--------------------|-------------|----------------------------|
| CR                 | No          | CR                         |
| Non-CR/non-PD      | No          | Non-CR/non-PD a |
| Not all evaluated  | No          | NE                         |
| Unequivocal PD     | Yes or No   | PD                         |
| Any                | Yes         | PD                         |

CR = complete response, PD = progressive disease, and NE = inevaluable.

A 'Non-CR/non-PD' is preferred over 'stable disease' for non-target disease since SD is increasingly used as endpoint for assessment of efficacy in some trials so to assign this category when no lesions can be measured is not advised.

**Table 3-3. The best overall response is when confirmation of CR and PR is required.**

| Overall response
First-time point | Overall response
Subsequent time point | Best overall response                                           |
|--------------------------------------|-------------------------------------------|-----------------------------------------------------------------|
| CR                                   | CR                                        | CR                                                              |
| CR                                   | PR                                        | SD, PD or PR a                                       |
| CR                                   | SD                                        | SD provided minimum criteria for SD duration met; otherwise, PD |
| CR                                   | PD                                        | SD provided minimum criteria for SD duration met; otherwise, PD |
| CR                                   | NE                                        | SD provided minimum criteria for SD duration met; otherwise, PD |
| PR                                   | CR                                        | PR                                                              |
| PR                                   | PR                                        | PR                                                              |
| PR                                   | SD                                        | SD                                                              |
| PR                                   | PD                                        | SD provided minimum criteria for SD duration met; otherwise, PD |
| PR                                   | NE                                        | SD provided minimum criteria for SD duration met; otherwise, NE |
| NE                                   | NE                                        | NE                                                              |

CR = complete response, PR = partial response, SD = stable disease, PD = progressive disease, and NE = inevaluable.

a If a CR is truly met at the first time point, then any disease seen at a subsequent time point, even a disease meeting PR criteria relative to baseline, makes the disease PD at that point (since the disease must have reappeared after CR). The best response would depend on whether the minimum duration for SD was met. However, sometimes 'CR' may be claimed when subsequent scans suggest small lesions were likely still present and, in fact, the patient had PR, not CR, at the first time point. Under these circumstances, the original CR should be changed to PR, and the best response should be PR.

#### Appendix 4: New York Heart Association (NYHA) Functional Classification

| Class | Description                                                                                                                                                               |
|-------|---------------------------------------------------------------------------------------------------------------------------------------------------------------------------|
| 0     | No heart disease                                                                                                                                                          |
| I     | No limitation on physical activity. Ordinary physical activity does not cause undue fatigue, palpitation (feeling heartbeats), or dyspnea (shortness of breath)           |
| II    | Slight limitation of physical activity. Comfortable at rest, but ordinary physical activity results in fatigue, palpitation, or dyspnea                                   |
| III   | Marked limitation of physical activity. Comfortable at rest, but less than ordinary activity causes fatigue, palpitation, or dyspnea                                      |
| IV    | Unable to carry out any physical activity without discomfort. Symptoms of cardiac insufficiency at rest. If any physical activity is undertaken, discomfort is increased. |

## Appendix 5: Case Report Form (English version)

### Patient General Information Questionnaire

No.:

Date:

Dear Patient,

Hello! Thank you for your trust in our hospital. To better understand your health condition and provide you with more comprehensive healthcare management services, we have designed this questionnaire. We kindly ask for your cooperation in completing it. The information you provide will be used solely for research purposes, and your personal privacy will be strictly protected.

Please read each question carefully and answer truthfully based on your actual situation. Your responses are crucial to the conclusions of our study. We sincerely appreciate your cooperation!

Thank you very much!

#### I. General Information

1. Gender: ① Male ② Female

2. Ethnicity: ① Han ② Other (please specify): \_\_\_\_\_

3. Age: \_\_\_\_\_ years

4. Education Level:

① Primary school or below ② Junior high school

③ High school / Technical secondary school / College ④ Bachelor's degree or above

5. Marital Status:

① Single ② Married ③ Divorced or widowed

6. Occupation Before Illness:

① Farmer ② Worker ③ Civil servant ④ Self-employed ⑤ Unemployed

⑥ Retired ⑦ Other (please specify): \_\_\_\_\_

7. Employment Status After Illness:

① Employed ② Unemployed ③ Retired

8. Monthly Household Income per Capita (RMB):

① <1,000 ② 1,000–2,999 ③ 3,000–4,999 ④ ≥5,000

9. Medical Payment Method:

- ① Self-paid ② Commercial insurance ③ Urban employee medical insurance  
④ Urban resident medical insurance ⑤ Other (please specify): \_\_\_\_\_

10. Primary Caregiver:

- ① Spouse ② Children ③ Parents  
④ Other (please specify): \_\_\_\_\_

II. Disease-Related Information

1. Disease Site:

- ① Nasopharynx ② Nasal cavity & paranasal sinuses ③ Larynx & hypopharynx ④  
Oral cavity ⑤ Major salivary glands ⑥ Oropharynx ⑦ Other (please specify): \_\_\_\_\_

2. Stage:

- ① Stage I ② Stage II ③ Stage III ④ Stage IV

3. ECOG Performance Status:

- ① 0 ② 1 ③ 2

4. Current Weight (kg): \_\_\_\_\_ (Assessed weekly)

5. BMI (kg/m^2): \_\_\_\_\_

# Scale I: QLQ-C30 Quality of Life Questionnaire

[figure not shown]

## EORTC QLQ-C30 (version 3)

We are interested in some things about you and your health. Please answer all of the questions yourself by circling the number that best applies to you. There are no "right" or "wrong" answers. The information that you provide will remain strictly confidential.

Today's date (Day, Month, Year): 

|  |  |  |  |  |  |  |  |
|--|--|--|--|--|--|--|--|
|  |  |  |  |  |  |  |  |
|--|--|--|--|--|--|--|--|

|                                                                                                          | Not at
All | A
Little | Quite
a Bit | Very
Much |
|----------------------------------------------------------------------------------------------------------|---------------|-------------|----------------|--------------|
| 1. Do you have any trouble doing strenuous activities, like carrying a heavy shopping bag or a suitcase? | 1             | 2           | 3              | 4            |
| 2. Do you have any trouble taking a long walk?                                                    | 1             | 2           | 3              | 4            |
| 3. Do you have any trouble taking a short walk outside of the house?                              | 1             | 2           | 3              | 4            |
| 4. Do you need to stay in bed or a chair during the day?                                                 | 1             | 2           | 3              | 4            |
| 5. Do you need help with eating, dressing, washing yourself or using the toilet?                         | 1             | 2           | 3              | 4            |

### During the past week:

|                                                                                | Not at
All | A
Little | Quite
a Bit | Very
Much |
|--------------------------------------------------------------------------------|---------------|-------------|----------------|--------------|
| 6. Were you limited in doing either your work or other daily activities?       | 1             | 2           | 3              | 4            |
| 7. Were you limited in pursuing your hobbies or other leisure time activities? | 1             | 2           | 3              | 4            |
| 8. Were you short of breath?                                                   | 1             | 2           | 3              | 4            |
| 9. Have you had pain?                                                          | 1             | 2           | 3              | 4            |
| 10. Did you need to rest?                                                      | 1             | 2           | 3              | 4            |
| 11. Have you had trouble sleeping?                                             | 1             | 2           | 3              | 4            |
| 12. Have you felt weak?                                                        | 1             | 2           | 3              | 4            |
| 13. Have you lacked appetite?                                                  | 1             | 2           | 3              | 4            |
| 14. Have you felt nauseated?                                                   | 1             | 2           | 3              | 4            |
| 15. Have you vomited?                                                          | 1             | 2           | 3              | 4            |
| 16. Have you been constipated?                                                 | 1             | 2           | 3              | 4            |

Please go on to the next page

**During the past week:**

|                                                                                                             | Not at
All | A
Little | Quite
a Bit | Very
Much |
|-------------------------------------------------------------------------------------------------------------|-----------------------|---------------------|------------------------|----------------------|
| 17. Have you had diarrhea?                                                                                  | 1                     | 2                   | 3                      | 4                    |
| 18. Were you tired?                                                                                         | 1                     | 2                   | 3                      | 4                    |
| 19. Did pain interfere with your daily activities?                                                          | 1                     | 2                   | 3                      | 4                    |
| 20. Have you had difficulty in concentrating on things,
like reading a newspaper or watching television? | 1                     | 2                   | 3                      | 4                    |
| 21. Did you feel tense?                                                                                     | 1                     | 2                   | 3                      | 4                    |
| 22. Did you worry?                                                                                          | 1                     | 2                   | 3                      | 4                    |
| 23. Did you feel irritable?                                                                                 | 1                     | 2                   | 3                      | 4                    |
| 24. Did you feel depressed?                                                                                 | 1                     | 2                   | 3                      | 4                    |
| 25. Have you had difficulty remembering things?                                                             | 1                     | 2                   | 3                      | 4                    |
| 26. Has your physical condition or medical treatment
interfered with your family life?            | 1                     | 2                   | 3                      | 4                    |
| 27. Has your physical condition or medical treatment
interfered with your social activities?      | 1                     | 2                   | 3                      | 4                    |
| 28. Has your physical condition or medical treatment
caused you financial difficulties?                  | 1                     | 2                   | 3                      | 4                    |

**For the following questions please circle the number between 1 and 7 that best applies to you**

29. How would you rate your overall health during the past week?

1            2            3            4            5            6            7

Very poor

Excellent

30. How would you rate your overall quality of life during the past week?

1            2            3            4            5            6            7

Very poor

Excellent

[figure not shown]

## **EORTC QLQ - H&N35**

Patients sometimes report that they have the following symptoms or problems. Please indicate the extent to which you have experienced these symptoms or problems during the past week. Please answer by circling the number that best applies to you.

| During the past week:                        | Not
at all | A
little | Quite
a bit | Very
much |
|-----------------------------------------------------|-----------------------|---------------------|------------------------|----------------------|
| 31. Have you had pain in your mouth?                | 1                     | 2                   | 3                      | 4                    |
| 32. Have you had pain in your jaw?                  | 1                     | 2                   | 3                      | 4                    |
| 33. Have you had soreness in your mouth?            | 1                     | 2                   | 3                      | 4                    |
| 34. Have you had a painful throat?                  | 1                     | 2                   | 3                      | 4                    |
| 35. Have you had problems swallowing liquids?       | 1                     | 2                   | 3                      | 4                    |
| 36. Have you had problems swallowing pureed food?   | 1                     | 2                   | 3                      | 4                    |
| 37. Have you had problems swallowing solid food?    | 1                     | 2                   | 3                      | 4                    |
| 38. Have you choked when swallowing?                | 1                     | 2                   | 3                      | 4                    |
| 39. Have you had problems with your teeth?          | 1                     | 2                   | 3                      | 4                    |
| 40. Have you had problems opening your mouth wide?  | 1                     | 2                   | 3                      | 4                    |
| 41. Have you had a dry mouth?                       | 1                     | 2                   | 3                      | 4                    |
| 42. Have you had sticky saliva?                     | 1                     | 2                   | 3                      | 4                    |
| 43. Have you had problems with your sense of smell? | 1                     | 2                   | 3                      | 4                    |
| 44. Have you had problems with your sense of taste? | 1                     | 2                   | 3                      | 4                    |
| 45. Have you coughed?                               | 1                     | 2                   | 3                      | 4                    |
| 46. Have you been hoarse?                           | 1                     | 2                   | 3                      | 4                    |
| 47. Have you felt ill?                              | 1                     | 2                   | 3                      | 4                    |
| 48. Has your appearance bothered you?               | 1                     | 2                   | 3                      | 4                    |

Please go on to the next page

| During the past week: |                                                                      | Not
at all | A
little | Quite
a bit | Very
much |
|------------------------------|----------------------------------------------------------------------|-----------------------|---------------------|------------------------|----------------------|
| 49.                          | Have you had trouble eating?                                         | 1                     | 2                   | 3                      | 4                    |
| 50.                          | Have you had trouble eating in front of your family?                 | 1                     | 2                   | 3                      | 4                    |
| 51.                          | Have you had trouble eating in front of other people?                | 1                     | 2                   | 3                      | 4                    |
| 52.                          | Have you had trouble enjoying your meals?                            | 1                     | 2                   | 3                      | 4                    |
| 53.                          | Have you had trouble talking to other people?                        | 1                     | 2                   | 3                      | 4                    |
| 54.                          | Have you had trouble talking on the telephone?                       | 1                     | 2                   | 3                      | 4                    |
| 55.                          | Have you had trouble having social contact with your family?         | 1                     | 2                   | 3                      | 4                    |
| 56.                          | Have you had trouble having social contact with friends?             | 1                     | 2                   | 3                      | 4                    |
| 57.                          | Have you had trouble going out in public?                            | 1                     | 2                   | 3                      | 4                    |
| 58.                          | Have you had trouble having physical contact with family or friends? | 1                     | 2                   | 3                      | 4                    |
| 59.                          | Have you felt less interest in sex?                                  | 1                     | 2                   | 3                      | 4                    |
| 60.                          | Have you felt less sexual enjoyment?                                 | 1                     | 2                   | 3                      | 4                    |

| During the past week: |                                                                  | No | Yes |
|------------------------------|------------------------------------------------------------------|-----------|------------|
| 61.                          | Have you used pain-killers?                                      | 1         | 2          |
| 62.                          | Have you taken any nutritional supplements (excluding vitamins)? | 1         | 2          |
| 63.                          | Have you used a feeding tube?                                    | 1         | 2          |
| 64.                          | Have you lost weight?                                            | 1         | 2          |
| 65.                          | Have you gained weight?                                          | 1         | 2          |

## Scale II: Nutrition Risk Screening (NRS-2002)

| Category                                      | Content                                                                                                                                                                           | Score |
|-----------------------------------------------|-----------------------------------------------------------------------------------------------------------------------------------------------------------------------------------|-------|
| 1. Disease Severity Score              | Pelvic fracture or chronic disease patients with any of the following: cirrhosis, COPD, long-term hemodialysis, diabetes, cancer.                                                 | 1     |
|                                               | Major abdominal surgery, stroke, severe pneumonia, hematologic malignancies.                                                                                                      | 2     |
|                                               | Traumatic brain injury, bone marrow suppression, ICU patients (APACHE >10).                                                                                                       | 3     |
|                                               | Subtotal                                                                                                                                                                   |       |
| 2. Impaired Nutritional Status Score   | Normal nutritional status, BMI $\geq 18.5$ , no weight change in the past 1–3 months, no change in food intake in the past week.                                                  | 0     |
|                                               | Weight loss >5% in the past 3 months or 20%–50% reduction in food intake (compared to requirements) in the past week.                                                             | 1     |
|                                               | Weight loss >5% in the past 2 months or BMI 18.5–20.5 or 50%–75% reduction in food intake (compared to requirements) in the past week.                                            | 2     |
|                                               | Weight loss >5% in the past month (or >15% in 3 months) or BMI <18.5 (or serum albumin <35 g/L) or 70%–100% reduction in food intake (compared to requirements) in the past week. | 3     |
|                                               | Subtotal                                                                                                                                                                   |       |
| 3. Age Score                           | Age $\geq 70$ years                                                                                                                                                               | 1     |
| Total Nutritional Risk Screening Score |                                                                                                                                                                                   |       |

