| Patient-Generated Subjective Global Assessment (PG-SGA) | Baseline (pre-radiotherapy) and weekly from radiotherapy initiation through the first-month post-treatment, followed by evaluations at 2, 3, and 6 months post-treatment.               |
| Distress Thermometer (DT)                               | Baseline (pre-radiotherapy) and weekly from radiotherapy initiation through the first-month post-treatment, followed by evaluations at 2, 3, and 6 months post-treatment.               |
| Patient Health Questionnaire-9 (PHQ-9)                  | Baseline (pre-radiotherapy) and once every two weeks from radiotherapy initiation through the first-month post-treatment, followed by evaluations at 2, 3, and 6 months post-treatment. |
| Hospital Anxiety and Depression Scale (HADS)            | Baseline (pre-radiotherapy) and once every two weeks from radiotherapy initiation through the first-month post-treatment, followed by evaluations at 2, 3, and 6 months post-treatment. |

- Quality control of questionnaire evaluations

To standardize questionnaire evaluations, we utilized video tutorials to assist patients in better understanding the self-rating questionnaires (EORTC QLQ-C30, EORTC QLQ-

H&N35, PG-SGA, DT, PHQ-9, HADS), enabling more accurate survey completion. For examiner-rated questionnaires (NRS 2002), nurses underwent collective training on the questionnaire content. They then conducted evaluations using standard patients to identify scoring discrepancies among different questionnaire-assessed nurses. This process enhanced understanding of the questionnaire content and reduced errors in examiner ratings.

For nutritional interventions, patients with an NRS 2002 score below 3 and a PG-SGA score below 4 were classified as having no or mild malnutrition. These patients received dietary guidance while continuing scheduled radiotherapy. For patients with a PG-SGA score of 4 or higher, different approaches were taken: those in the control group were referred to the nutrition department for consultation. In contrast, patients in the experimental group were coordinated by the risk-stratified nurses to receive individualized treatment from SHINE-MDT.

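### The NRS-2002 form scores a stable patient with BMI 18.5–20.5 as both 0 and 2, so the total can fall on either side of the cut-off of 3

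*Protocol*

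**What the plan says.** Scale II in Appendix 5 adds three parts: disease severity, impaired nutritional status and age.

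- **Disease severity.** The 1-point row reads "Pelvic fracture or chronic disease patients with any of the following: cirrhosis, COPD, long-term hemodialysis, diabetes, cancer". Every enrolled patient has cancer and so has at least 1 point.
- **Nutritional status, 0 points.** BMI of 18.5 or more, with "no weight change in the past 1–3 months, no change in food intake in the past week".
- **Nutritional status, 1 point.** Weight loss above 5% in 3 months, or intake reduced by 20–50%.
- **Nutritional status, 2 points.** "Weight loss >5% in the past 2 months or BMI 18.5–20.5 or 50%–75% reduction in food intake". The criteria are joined by *or*, so the BMI range is enough by itself.
- **Nutritional status, 3 points.** Among other criteria, "70%–100% reduction in food intake (compared to requirements) in the past week".
- **Age.** 1 point from age 70.

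Section 3.2 (quality control of questionnaire evaluations) then states that "patients with an NRS 2002 score below 3 and a PG-SGA score below 4 were classified as having no or mild malnutrition". The next step in care is worded on the other scale: "For patients with a PG-SGA score of 4 or higher, different approaches were taken". Sections 2 and 4.3 name NRS 2002 as a measure of the secondary objective on nutritional status.

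**The concern.** The 0-point and 2-point rows contradict each other for BMI 18.5–20.5. If weight and intake are stable, the form calls the same patient normal and impaired. Neighbouring intake bands share values as well: 50% lies in the 1- and 2-point rows, and 70–75% in the 2- and 3-point rows. Nothing printed on the form says which row prevails.

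NRS 2002 is rated by nurses and repeated weekly during radiotherapy. Two nurses who follow the form correctly could record totals 2 points apart for the same patient. That adds avoidable noise to a named secondary measure. It also leaves membership of the no-or-mild-malnutrition class undetermined for some patients.

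**Working it through.** The Protocol states no figure to reproduce here; the check is one of scoring logic.

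**Inputs, all from Scale II:** disease severity 1 (cancer, with no higher disease item present); nutritional points from each row that the patient meets; age 0, or 1 from age 70. Albumin is taken as 35 g/L or above, so that it does not trigger the 3-point row. The cut-off of 3 comes from section 3.2.

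**Formula:** total = disease severity + nutritional status + age.

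| Profile | Rows met | Under 70 | 70 or over | Crosses 3? |
|---|---|---|---|---|
| BMI 21, stable weight and intake | 0 | 1+0+0 = 1 | 1+0+1 = 2 | Single value |
| BMI 18.5–20.5, stable weight and intake | 0 and 2 | 1+0+0 = 1 or 1+2+0 = 3 | 1+0+1 = 2 or 1+2+1 = 4 | Yes, at any age |
| BMI 23, stable weight, intake down 50% | 1 and 2 | 1+1+0 = 2 or 1+2+0 = 3 | 1+1+1 = 3 or 1+2+1 = 4 | Only under 70 |
| BMI 23, stable weight, intake down 70–75% | 2 and 3 | 1+2+0 = 3 or 1+3+0 = 4 | 1+2+1 = 4 or 1+3+1 = 5 | No |

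The BMI conflict is the largest. It covers a whole interval of values, moves the total by 2 points and crosses the cut-off at every age. The 50% conflict is a single boundary value worth 1 point. The 70–75% conflict changes the score by 1 point but never the side of the cut-off.

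**Consequence under section 3.2.** The class requires "patients with an NRS 2002 score below 3 and a PG-SGA score below 4".

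- With PG-SGA below 4, choosing row 0 or row 2 decides whether the patient is in the class. The text of section 3.2 does not say how a patient with NRS of 3 or more and PG-SGA below 4 is handled.
- With PG-SGA of 4 or higher, the patient is outside the class and meets the trigger whatever the NRS total.

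**The case against.** The best defence is that the form implies its own rule. The weight-loss criteria are nested: a loss above 5% in one month also meets the 2-month and 3-month criteria, so the scale works only if the highest row is taken. On that reading BMI 19.5 scores 2 and every overlap resolves to one value. In addition, section 3.2 describes collective training of the nurses and rating of standard patients to find scoring discrepancies. The profile is also narrow. It needs stable weight and unchanged intake, in a population for which section 1 cites malnutrition rising from 24% before radiotherapy to 88% after it. The BMI conflict may therefore arise mostly at baseline.

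Much of this stands as a limit on size. It does not remove the defect. The highest-row rule is not printed, and even with it the 0-point row would still describe a patient with BMI 19.5 as normal. Training may have produced a convention, but the Protocol records none that settles these overlaps.

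A reader might also infer that the score drifts between arms. The documents do not support that. They describe one form and one training process, and do not say whether the raters were blinded. Drift by arm is possible but speculative.

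**Conclusion.** The point holds as a contradiction in the printed form, with limited reach. For BMI 18.5–20.5 with stable weight and intake the total is 1 or 3 (2 or 4 from age 70), on either side of 3. For an intake reduction of 50% it is 2 or 3 under age 70. The NRS secondary outcome and the no-or-mild-malnutrition class are affected, the latter only where PG-SGA is below 4.

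The text of section 3.2 ties referral or team care to PG-SGA of 4 or higher, sections 2 and 4.3 define no endpoint at NRS of 3 or more, and neither the primary endpoint nor the sample size uses the scale. This rests on the text alone, because the nutritional flow charts (eFigures 2 and 4) could not be read. The number of affected patients is unknown.

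One stronger reading is tempting. The 3-point disease-severity row includes "Traumatic brain injury, bone marrow suppression, ICU patients (APACHE >10", and the trial gives cisplatin, so a reader might conclude that the score wrongly measures chemotherapy toxicity. The form is unambiguous on that item. Whether the item is misplaced depends on the source instrument, which is not among the documents, and nothing in them says that a treatment-related fall in blood counts is to be scored there. It is not part of this finding.

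**What to change.** 1. Reconcile the BMI limits of the 0- and 2-point rows, and the boundaries of the intake bands, so that each value falls in one row. The choice of limits should be checked against the instrument's source.
2. Print on the form that the highest row met is scored, and apply this identically in both arms.
3. Reconcile the form with the classification in section 3.2, so that every NRS and PG-SGA combination has a stated class.
4. Re-score the BMI component by program from the recorded weight and BMI. The case report form holds both, with weight assessed weekly.
5. Where percentage intake was not recorded, keep the recorded intake score and say so in the report. A full re-score should not be promised: the forms shown have no percentage-intake field, and PG-SGA records intake only in categories.

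The cost is one corrected form page, a small amount of re-scoring work and some changed NRS totals. The residual intake ambiguity remains in data already collected and should be reported as a limitation.
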